### Movement/posture

Besides muscle activation, the upper-body exoskeletons should be able to optimize movements and reduce physical stress. A full-body analysis during an overhead task was executed by Latella et al. (34) showing a significant reduction in internal full-body moments ranging from 66 to 86%. Furthermore, internal joints loads were found to be decreased as well in the shoulder and trunk area. However, this decrease was compensated by general increase in the load on the legs because internal strains intuitively transfer to the lower body, particularly the hips.

### Cognitive-motor interference

Next, to the movement aspects, the use of exoskeletons involves a complex interplay between users and the support system, encompassing psychological and physical elements in human-machine interaction (HMI) or cognitive-motor interference. This interaction is often observed in scenarios requiring the concurrent execution of tasks, involving cognitive and/or motor resources and leading to cognitive-motor interference [CMI; (35)]. CMI, characterized by performance decline in dual-task situations, may incur dual-task costs (36). Various models, rooted in the principles that performance quality is tied to processing activity quantity, and this processing is inherently limited, provide insights into the concept of CMI (37). Initial studies have delved into cognitive load associated with exoskeleton use across various contexts, unveiling CMI effects that impact pace and reaction times [e.g., (38)]. Evidence indicates that exoskeleton use requires heightened effort in terms of motor adaptation and neurocognitive control. Factors such as cognitive load, cognitive-motor process complexity, demographic variables, and exoskeleton characteristics contribute to CMI. Recent reviews corroborate the impact of upper-limb exoskeletons on cognitive workload and physical performance. In a study by Taygi et al. (33), neurophysiological adaptations during exoskeleton use were investigated. Their research uncovered variations in neural activity and functional connectivity within the primary motor cortex, offering valuable insights into the influence of exoskeletons on the nervous system. In the realm of exoskeleton research, a meticulous exploration of the discomfort aspect has yielded valuable insights from several studies. For example, Otten et al. (9) presented noteworthy findings, revealing a tangible decrease in overall task effort with the implementation of the Lucy exoskeleton. This reduction suggests a potential ergonomic advantage associated with exoskeleton use.

### Postural discomfort

Despite all potential benefits of exoskeleton use, De Bock et al.'s (39) investigation added complexity to the understanding of discomfort, uncovering shifts and heightened frustration among exoskeleton users. Interestingly, this discomfort was accompanied by a simultaneous reduction in temporal workload, indicating a nuanced interplay of factors influencing user experience. In a separate study, Borrel Rubio and Mora Quiles (40) delved into the ergonomics of a shoulder exoskeleton during overhead assembly tasks with findings of a reduction in shoulder joint moments, indicating positive strides in enhancing user comfort. The integration of the NASA TLX questionnaire further enriched the analysis, revealing diminished perceived physical demand and a marginal reduction in mental effort. Contrary, Weston et al. (41) found slightly higher overall discomfort while using an upper-body exoskeleton during overhead tasks. Additionally, Giustetto et al. (42) found that the effect of the exoskeleton on comfort/discomfort differs in different parts of the body. For example, the exoskeleton was able to reduce discomfort in the lumbar spine region while increasing discomfort in the chest and feet. These studies therefore show that it may not be possible to increase the comfort level for all body regions.

Depending on these interdisciplinary considerations, an exoskeleton might influence cognitive and motor performance via different pathways: it would be possible that cognitive resources are given free due to physical assistance with decreased physical demands and reduced exhaustion or reflecting motor control theories, the additional use and wearing of an exoskeleton needs to be integrated into automatized movements and therefore might need more cognitive resources.

Therefore, the aim of this study is to advance our understanding of exoskeleton effects by conducting inclusive research, addressing cross-gender comparisons, and exploring the impact on cognitive and physical workload within real-world scenarios. Based on these objectives, we define the following questions with the focus on gender differences:

Are there gender effects of using an upper body exoskeleton for both tasks regarding:Muscle synergies?Upper body posture?Cognitive resources?Comfort/discomfort, acceptance and usability?Are there gender effects of using an upper body exoskeleton for both tasks under previous physical fatigue for:Muscle synergy?Upper body posture?Cognitive resources?

The research questions will be answered using a randomized crossover study design (*cf.*
Figures 1, 2). Participants of each gender will be randomly assigned to different sequences of interventions, ensuring a balanced distribution of order effects. This design allows each participant to serve as their control, contributing to internal validity.

**Figure 1 fig1:**
[figure not shown]
Study flow of the precision task (nailing following the Fitts paradigm).

**Figure 2 fig2:**
[figure not shown]
Study flow of the physical performance task (PILE task).

## Methods and analysis

### Trial design

This study includes a randomized experimental cross-sectional design comparing males and females (parallel groups). This means that each participant runs through each scenario in a randomized order.

### Study setting

The study will be conducted as a monocentric study at the University of Hamburg (Germany). For the experiments a specific workstation is installed to secure the ecological validity.

### Exoskeleton being used

This study will conduct the experiments using the battery powered, pneumatic exoIQ (name of the company) S700 active Exoskeleton. The S700 is purposefully designed to support during manual tasks in and above shoulder height and is commercially available from 2023. It can be adjusted to fit both men and women from between 1.65 m up to 2.05 m body height and with various body types. Both, the amount of supporting torque and the characteristics of its application during use (torque curve) can be altered to the demands of user and task. These alterations are being stored on the device via presets. For each task, a specified preset will be used and the amount of support torque will be adjusted to the individual need.

### Eligibility criteria

Participants should be within the age range of 18–45 years, between 1.65 m and 2.05 m body height and do not have any chronic physical or mental health disorders.

The experiments will be executed by trained sports scientists with at least a Bachelor degree.

### Experimental set-up/intervention

The experimental design includes two physical tasks (1. Physical Performance Task and 2. Precision Task) in four randomized conditions (with and without exoskeleton and with and without prior physical fatigue; *cf.*
Figures 1, 2):

Physical Performance Task (PILE task) at shoulder height:Participants will perform the Physical Performance Task at shoulder height, both with and without the exoskeleton. This task aimed to assess the impact of the exoskeleton on physical performance under normal working conditions.

Precision Task (nailing following the Fitts paradigm) at overhead height:The Precision Task involves overhead nailing activities following the Fitts paradigm (43, 44) (three predefined templates into which the nails must be precisely inserted.), simulating tasks requiring precision and skill. Participants will execute this task with and without the exoskeleton, allowing the evaluation of the exoskeleton’s influence on tasks demanding fine motor skills.

Randomization will be done by the online program www.randomizer.org.

### Experimental procedure

#### Precision task (nailing following the Fitts paradigm)

The Precision Task consists of simulating overhead nailing work during a work process. The nails are shot overhead into a device using a nail gun. The process can be compared, for example, with screwing or drilling processes in industrial or craft areas. The Einhell TE_CN 18-Solo cordless nailer will be used.

The Precision task includes the following sequence [*cf.* (43)]: The subjects stand under the setup. To determine the height of the fixture, the test subjects will be asked to bring the pistol into contact with the wooden plate with the elbow at acromion level. The time will be measured by the start signal of the measuring supervisor and the test person begins the task. The aim is to try to hit the target (Fitts task) as quickly and accurately as possible with the nail gun so that a visible imprint will be made on the paper. If a field is missed, the measuring supervisor instructs the participants to retrieve it. As soon as a template is completed, the time will be stopped, errors noted and it is replaced by the next template (Fitts task). The standardized break between the three patterns is 30 s. After another start signal, the task and timing will be repeated until all three templates are completed. There are two conditions, which are performed at random with the exoskeleton and without the exoskeleton.

#### Physical performance task (PILE task)

The PILE task, which was developed by Mayer et al. (45), is a functional assessment tool for measuring manual lifting ability. It involves lifting a weighted box in four movement cycles from a starting position to two predetermined heights: from the floor to hip height and from the hip to shoulder height. The task assesses cardiovascular endurance, overall lifting capacity, psychophysical fatigue of the trunk and limbs and motivational factors through repeated lifting cycles. During the task, the weight is increased after each successful cycle, starting at 4 kg for women and 6 kg for men. The total test duration is approximately 10–15 min. The aim is to assess lifting ability for specific heights, taking into account the maximum weight lifted, time to abort and heart rate at abort. The aim of the task is to calculate the work performed and the strength. The PILE task shows a high test–retest reliability with correlation coefficients of r = 0.87 for lifting at hip height and r = 0.93 for lifting at shoulder height (*p* < 0.001). Termination criteria include psychophysiological factors, aerobic capacity exceeding 85% of maximum heart rate, and safety concerns related to exceeding a predetermined weight limit. Normative values for test performance are calculated based on age, height and weight, with age influencing the calculation of aerobic capacity and height determining the tolerable lifting capacity. For this study purpose, we only use the hip to shoulder height task.

#### Physical fatigue session

A fatigue session takes place, following a randomized order, e.g., before the PILE task or before the nailing task. The fatigue session will be performed in 3 sets, with a 2-min calf raise and a 2-min front raise with weight per set, with the front raise in the second set only being performed for the second minute. The weight of the men is 5 kg and that of the women 2.5 kg. There will be a break of 60 s between the sets. During the exercise, a metronome runs at 60 bpm, and the front and calf raises are to be performed to this beat. Before the start of the fatigue session, the maximum body height will be determined individually on the anthropometer by the test person standing upright and bringing their feet into plantar flexion. This determined height should be reached during each exercise. The level of fatigue will be determined using EMG power spectral shifts (Fast Fourier Transform) in combination with a visual analog scale of peripheral fatigue.

Questionnaires on acceptance and discomfort of the conditions with exoskeleton use will be filled out after the experimental procedure.

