#### Speed accuracy trade offs (Fitts task)

The Fitts task is a standard motor control experiment in which participants move quickly between two targets of different sizes and distances (44). The aim is to assess the speed and accuracy of the target movements. The difficulty of the task is determined by a difficulty index, which is calculated based on the size and distance of the targets. The researchers manipulate the task conditions to investigate factors that influence movement time and accuracy. Key measures include movement time and error rate, which provide insight into the trade-off between speed and accuracy in motor control. The Fitts task is often used in human-computer interaction and to assess motor skills.

The Borg rating of perceived exertion is used together with the SUS and the NASA-TLX questionnaires to answer research question 1d, investigating the effects of using an upper body exoskeleton on comfort/discomfort, acceptance and ease of use during task performance.

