#### Subjective perceived exertion (Borg-scale)

The subjective assessment of the perceived exertion is carried out by using the 15-point Borg scale (6–20) after each test session. 6 points equal very very low exertion, and 20 points equal very very high exertion (49). The assessment refers to the overall perceived exertion and specific body regions, such as the neck, shoulders, arms, upper and lower back, and legs. A chart is shown for this purpose.

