#### Subjective workload assessment questionnaire

The Subjective workload assessment questionnaire (NASA-Task Load Index, NASA-TLX) addresses the technical part of the experiment, capturing workload at multiple levels, regarding the interaction with the exoskeleton: mental demands, physical demands, time demands, performance, effort, and frustration (50).

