### Participant timeline

The study will be conducted over two separate days to mitigate potential carryover effects and ensure the avoidance of additional fatigue symptoms. On each day, participants will undergo the assigned conditions for both tasks in a randomized order, minimizing the impact of confounding variables. The sequence of conditions will be counterbalanced across participants to control for order effects.

First, the participants are welcomed and informed in writing and verbally about the aim and conduct of the study. This is followed by the recording of the anthropometric data and personal data. Then the preparations for the surface electromyography begin, including the application of the electrodes and the pre-tests (MVC). The suit for the Xsens sensors is then applied and a calibration is carried out. Finally, the sensor and the calibration for the fNIRS are carried out.

The first session then begins, depending on which task was selected first for the person. The person is then either fitted with the exoskeleton and begins the first task (Physical Performance Task or Precision Task) or performs this without the exoskeleton. If the fatigue protocol is already planned for the person at the beginning based on the randomization, this is carried out without the exoskeleton before the start of the task.

After completion of the first task, an individual break is taken before the second task begins. After completing both tasks, the person is asked to complete the questionnaires.

Due to the activity of overhead work, which already involves increased exertion because of the non-ergonomic posture, and the additional activity of screwing, physical fatigue may increase. Therefore, physical exertion is subjectively documented via the Borg scale (49) after each test session. Additionally, test sessions are spread over 2 days.

Individual breaks will be provided between each test session due to possible mental and physical exertion during the tests (Figure 3).

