### Gender differences

With respect to the research questions, we hypothesize that potential gender differences will be observed within the muscle synergies. We think that the exoskeleton use will reduce shoulder muscle activity significantly [e.g., (54)] but first studies suggest that women might have less muscle activation in the shoulder muscles while wearing an exoskeleton (33). On the other hand, with respect to the design and the weight of the exoskeleton, women potentially could use different movement patterns to manage the tasks (56) due to differences in biomechanical and anthropometric trunk muscle geometry of females and males (56, 57). We anticipate that women show more bending backwards movements including a higher compensatory muscle activation in the abdominal and neck muscles. However, this idea has to be proven within our experimental design.

Moreover, as women are merely not integrated into the iterative designing processes of exoskeletons, yet, we propose more discomfort and less usability in the ratings by the women. This discomfort especially will be reported for the shoulder region (41).

In line with the cognitive resource theories (36), this discomfort might lead to more attentional resources spending on the discomfort and less resources available for the working DT situation. This will increase the cognitive-motor interference especially in the DT situation and could be observed with more cortical activation in the prefrontal cortex [*cf.* (35)]. Moreover, the working accuracy will decrease (58).

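### No discomfort rating without the exoskeleton is stated, so a gender difference arising from the task cannot be separated from a gender-specific effect of the device

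*Protocol article*

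**What the plan says.** Research question 1, at the end of the Introduction, asks for gender effects of using the exoskeleton. Item d covers comfort/discomfort, acceptance and usability. The Discussion (Gender differences) predicts more discomfort in women and adds: "This discomfort especially will be reported for the shoulder region".

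On measurement, the article says the following.

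- **Physical fatigue session, last paragraph:** "Questionnaires on acceptance and discomfort of the conditions with exoskeleton use will be filled out after the experimental procedure". Data management agrees, listing only comfort in using the device, by questionnaire.
- **Participant timeline:** "After completing both tasks, the person is asked to complete the questionnaires".
- **Speed accuracy trade offs (Fitts task), last paragraph:** "The Borg rating of perceived exertion is used together with the SUS and the NASA-TLX questionnaires to answer research question 1d". The sections that follow describe these instruments as measures of exertion, usability and workload. NASA-TLX is described as "capturing workload at multiple levels, regarding the interaction with the exoskeleton".
- **Abstract, Methods:** standardized questionnaires will cover postural comfort/discomfort as well as acceptance and usability.
- **Borg scale:** "The assessment refers to the overall perceived exertion and specific body regions, such as the neck, shoulders, arms, upper and lower back, and legs". The Participant timeline adds that "physical exertion is subjectively documented via the Borg scale (49) after each test session", with no restriction to exoskeleton conditions. The Statistical analysis section gives Borg a repeated measures ANOVA.

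**The concern.** The article justifies the crossover by saying that each participant acts as their own control. For discomfort, as the plan is written, that control is absent: the rating is tied to the exoskeleton conditions and nothing comparable is stated for the same work without the device.

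The gap matters because the work can be uncomfortable in itself. The Abstract names overhead work as a cause of musculoskeletal discomfort. Nor can equal discomfort in the two genders without the device be assumed. The PILE task starts at 4 kg for women and 6 kg for men, and the fatigue session uses 2.5 kg and 5 kg, so a difference in either direction is possible.

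If women report more shoulder discomfort with the exoskeleton, the trial could not say whether the device or the overhead work is responsible. If the task-related difference runs the other way, a real device effect could be hidden. No later analysis plan can repair this, because it cannot supply ratings that were never collected.

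**Working it through.** The plan states no figure for discomfort, so there is none to reproduce. The check has two parts.

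**1. What each design estimates.** Write *b* for the difference between women and men in discomfort from the task alone, and *d* for the additional difference that the device causes (the gender-by-exoskeleton effect). Assume that the two add.

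- Women minus men, with exoskeleton: *b* + *d*
- Women minus men, without exoskeleton: *b*
- Difference of the two: *d*

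Research question 1d and the shoulder hypothesis concern *d*. Ratings from exoskeleton conditions alone give only *b* + *d*.

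**2. How much this could matter.** Set *d* = 0 and ask how often exoskeleton-only ratings still give a significant gender difference.

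Inputs:
- *n* = 36 per gender and alpha = 0.05 (Sample size). Sidedness is not stated; two-sided is assumed.
- *b* in SD units: assumed, since the documents give no discomfort SD or gender difference.
- Test: two-sample t-test. This is also assumed, since the Statistical analysis section names no test for discomfort.

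Formula: noncentrality = *b* × √(*n*/2), with 2*n* − 2 degrees of freedom. For *n* = 36, √18 = 4.243 and there are 70 degrees of freedom.

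| Assumed *b* (SD) | Noncentrality (*n* = 36) | Chance of significance, *n* = 36 | *n* = 40 | *n* = 32 |
|---|---|---|---|---|
| 0 | 0 | 0.050 | 0.050 | 0.050 |
| 0.2 | 0.849 | 0.133 | 0.143 | 0.124 |
| 0.3 | 1.273 | 0.241 | 0.263 | 0.219 |
| 0.5 | 2.121 | 0.553 | 0.598 | 0.504 |
| 0.8 | 3.394 | 0.917 | 0.942 | 0.883 |

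The *n* = 40 column is the planned recruitment per gender. The *n* = 32 column is 40 × (1 − 0.20), that is, after the planned 20% loss.

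If the same scale is also given without the exoskeleton, *b* cancels from the with-minus-without contrast and the rate returns to 0.05 for every *b*. For ratings with equal variance σ² and within-person correlation ρ, that contrast has variance 2σ²(1 − ρ) per person, against σ² for a single rating. It is therefore also the more precise of the two when ρ exceeds 0.5, and the less precise when ρ is lower.

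**The case against.** The best defence is that discomfort here means discomfort from wearing the device. Data management speaks of comfort in using it, the Harms section says that wearing one may feel uncomfortable, and the hypothesis about women rests on their absence from exoskeleton design. If every item asks strictly about the device, comparing the genders' ratings answers much of the question directly. The item wording is not shown, so this cannot be excluded. It fits less well with the hypothesis about the shoulder, a region that overhead work loads with or without a device.

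A second defence is that the plan already has a regional, within-person rating. Borg covers the shoulders, follows each test session and is assigned to 1d, so a gender-by-exoskeleton test is available for exertion. That stands, and 1d as a whole does not lose the crossover. But exertion is a different construct from discomfort. The article's own Postural discomfort section cites a study in which an exoskeleton eased the lumbar region while increasing discomfort in the chest and feet.

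Four stronger readings are tempting, and the documents do not support them.

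- **Discomfort is rated only once, at the end.** Neither timing statement says so. Testing runs over two days, the questionnaires may follow both tasks on each day, and the figures with the schedule are not shown.
- **The fatigue part of the study fails for want of discomfort ratings.** Research question 2 does not list discomfort. The idea that fatigue weakens the discomfort effect appears only in the Discussion, which calls its hypotheses speculative. Testing that idea would need ratings by fatigue state; whether these are taken is not stated.
- **No instrument measures discomfort.** The sentence assigning instruments to 1d is not a complete list: it also omits the user acceptance items. A discomfort questionnaire is mentioned elsewhere, and its content may stand in the full protocol.
- **All of 1d is affected.** Acceptance and SUS usability have no meaning without the device.

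**Conclusion.** The point holds for the discomfort part of research question 1d and the shoulder-discomfort hypothesis. As written, discomfort is rated for exoskeleton conditions, no reference rating without the device is stated, and a gender difference in these ratings cannot be attributed to the exoskeleton.

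The size is illustrative. With 36 per gender and no gender-specific device effect, an assumed task-related difference of 0.2 to 0.5 SD produces a significant gender difference in 13% to 55% of studies, against 5% when there is no such difference. These figures rest on assumed values of *b*, an additive model and a t-test that the plan does not name. Discomfort is not the sample-size outcome. This is a cheap and worthwhile improvement, not a flaw in the trial's main comparison.

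There is also a smaller inconsistency. The paragraph assigning instruments to 1d names three that are described as measuring exertion, usability and workload, while the Abstract, the Physical fatigue session and Data management refer to questionnaires on comfort or discomfort.

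**What to change.** 1. Add a regional discomfort rating, including the shoulders, to the Borg body-region chart already shown after each test session. Collect it in the conditions with and without the exoskeleton.
2. Name the gender-by-exoskeleton interaction on shoulder discomfort as the test for the discomfort part of research question 1d.
3. Keep SUS and acceptance as ratings of the device only.
4. Reconcile the paragraph that assigns instruments to 1d with the Abstract, the Physical fatigue session and Data management, so that one named instrument measures discomfort. Do not present Borg, SUS or NASA-TLX as discomfort measures.
5. If the Discussion's idea about fatigue and discomfort is to be examined, record the rating by fatigue state as well; otherwise leave it labelled as speculation.

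The cost is about a minute more per run (an estimate, not a figure from the documents), slightly more burden on participants, and a short amendment to the questionnaires. The change has to be made before data collection, because missing ratings cannot be recovered afterwards.
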